### Secondary outcomes

#### MRI examinations

The MRI examinations (MAGNETOM version 3.0T MRI Scanner using head matrix coils; Siemens Medical Solutions, Erlangen, Germany) will be performed within 7 days and at 1 month after the onset of Bell’s palsy. The conventional MRI protocol for this study consists of the following sequences. Three-dimensional constructive interference in the steady state will be performed in an axial orientation with the following parameters: 18-cm field of view (FOV), repetition time/echo time (TR/TE) of 8.58/3.91 ms, 64 sections of 0.5-mm thickness, with a matrix of 320×320 pixels, flip angle 50 degrees, bandwidth of 460 Hz, and acquisition time of 6 minutes, 12 seconds. A volume-interpolated body examination will be performed in precontrast and contrast T1 with the following parameters: 18-cm FOV, TR/TE of 20/3.69 ms, 32 sections of 1-mm thickness, with a matrix of 320×320 pixels, flip angle 12 degrees, bandwidth of 130 Hz, and acquisition time of 3 minutes, 4 seconds. Gadolinium-diethylenetriamine pentaacetic acid (contrast medium) will be administered intravenously at a dosage of 0.1 mmol/kg.

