## Abstract

**Background:**

Although many patients with facial paralysis have obtained benefits or completely recovered after acupuncture or electroacupuncture therapy, it is still difficult to list intuitive evidence besides evaluation using neurological function scales and a few electrophysiologic data. Hence, the aim of this study is to use more intuitive and reliable detection techniques such as facial nerve magnetic resonance imaging (MRI), nerve electromyography, and F waves to observe changes in the anatomic morphology of facial nerves and nerve conduction before and after applying acupuncture or electroacupuncture, and to verify their effectiveness by combining neurological function scales.

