**Methods/Design:**

A total of 132 patients with Bell’s palsy (grades III and IV in the House-Brackmann [HB] Facial Nerve Grading System) will be randomly divided into electroacupuncture, manual acupuncture, non-acupuncture, and medicine control groups. All the patients will be given electroacupuncture treatment after the acute period, except for patients in the medicine control group. The acupuncture or electroacupuncture treatments will be performed every 2 days until the patients recover or withdraw from the study. The primary outcome is analysis based on facial nerve functional scales (HB scale and Sunnybrook facial grading system), and the secondary outcome is analysis based on MRI, nerve electromyography and F-wave detection. All the patients will undergo MRI within 3 days after Bell’s palsy onset for observation of the signal intensity and facial nerve swelling of the unaffected and affected sides. They will also undergo facial nerve electromyography and F-wave detection within 1 week after onset of Bell’s palsy. Nerve function will be evaluated using the HB scale and Sunnybrook facial grading system at each hospital visit for treatment until the end of the study. The MRI, nerve electromyography, and F-wave detection will be performed again at 1 month after the onset of Bell’s palsy.

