### Elimination criteria

Patients with cerebral infarction, cerebral hemorrhage, or other brain tumors diagnosed on the basis of skull computed tomography or MRI and patients who refuse to sign the written informed consent or did not coordinate with the randomized enrollment will be excluded from the study.

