### Acute stage

Patients in groups A and B will receive acupuncture therapy at the Cuanzhu (BL2), Yangbai (GB14), Sizhukong (TE23), Qianzheng, Yingxiang (LI20), Quanliao (SI18), Dicang (ST4), Hegu (LI4), and Taichong (LR3) points. The acupuncture points are identified according to the method of point location issued by the World Health Organization (WHO). The acupuncture needles will be inserted straightly or obliquely with a depth of 10–30 mm to bring about the desired sensation of *deqi* (see Table 2), and the needles will be left in place for 20 minutes. The acupuncture therapy will be performed once every 2 days. Accordingly, patients in group A (electroacupuncture in the acute stage) will receive electroacupuncture therapy at the Yangbai (GB14)-Sizhukong (TE23), Quanliao (SI18)-Yingxiang (LI20), and Qianzheng-Dicang (ST4) points (2 Hz, density wave, 20 minutes) once every 2 days. Patients in group C will not receive acupuncture therapy.

**Table 2 Tab2:** Acupuncture points and needle insertion procedures

Acupuncture point	Direction	Depth (mm)
GB14 (yangbai, affected side)	Transversely toward geisoma	20–30
SJ23 (sizhukong, affected side)	Obliquely toward partes temporalis	20–30
Qianzheng (extra point, affected side)	Perpendicular to the skin	20–30
LI20 (yingxiang, affected side)	Obliquely along nasolabial sulcus toward the root of the nose	20–30
SI18 (quanliao, affected side)	Perpendicular to the skin	20–30
ST4 (dicang, affected side)	Transversely toward ST6	10–20
LI4 (hegu, bilateral)	Perpendicular to the skin	20–30
LR3 (taichong, bilateral)	Perpendicular to the skin	20–30

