#### Facial nerve electromyography

The surface recording electrodes will be placed on the orbicularis oculi muscle and the orbicularis oris. The reference electrode will be placed on the nasal bone. The ground electrode will be placed on one arm. Super strong stimulations will be applied to the stylomastoid foramen, and the latency and amplitude of the motor evoked potentials (M wave) at the initial location will be observed, first on the unaffected side and then at the same location on the affected side. The results of the two sides will be compared. Meanwhile, the R1/M-wave ratio in latency will be measured. The measurements will be performed within 7 days and at 1 month after palsy onset.

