### Statistical analysis

In this study, statistical analyses of data will be performed by professionals rather than investigators using intention-to-treat and per-protocol approaches. All demographic and clinical characteristics of the subjects (such as sex, age) will be processed based on descriptive analyses. Quantitative data will be presented as average, standard deviation, median value, and range. Qualitative data will be presented as the frequency and percentage.

For the primary outcome measurements, a repeated-measures multifactorial analysis will be performed to identify differences between groups (differences within each group based on time, and the effects of the interaction of the variables based on group) to compare the differences in HB and Sunnybrook score changes between the interventional and control groups based on time (baseline, every treatment time and 1 month after palsy onset). The period from the onset to the first change in facial paralysis evaluation scale score in and the patients’ overall recovery period will be compared using one-way analysis of variance (ANOVA) between all groups. For the secondary outcome measurements, a χ^2^ test will be used to compare the edema onset frequency of the facial nerve on the affected side. One-way ANOVA will be applied to identify differences in results of facial nerve electromyography and F-wave detection between groups. In cases of non-normally distributed data, the Kruskal-Wallis H test will be performed.

All adverse events reported during the study will be included in the clinical report, and the prevalence of adverse events will then be calculated. The percentage of participants with adverse events in each group will be calculated and compared using the χ^2^ test or Fisher’s exact test. Statistical analyses will be performed using IBM SPSS for Windows version 19.0 statistical software (IBM, Armonk, NY, USA). All the tests will be two-sided, and a *P* value <0.05 will be considered statistically significant.

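### The first MRI, EMG and F-wave are timed from palsy onset, not from the first session, so the pre-treatment value can follow assigned treatment in groups A and B only; the MRI limit is also given as both 3 and 7 days

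*Protocol article*

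**What the plan says.** The abstract states the aim as observing "changes in the anatomic morphology of facial nerves and nerve conduction before and after applying acupuncture or electroacupuncture". The examinations meant to show this are MRI, facial nerve EMG and F-wave, each done twice.

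- **MRI, Methods (MRI examinations):** "will be performed within 7 days and at 1 month after the onset of" Bell's palsy.
- **MRI, abstract (Methods/Design):** "All the patients will undergo MRI within 3 days after" onset.
- **EMG, Methods:** "The measurements will be performed within 7 days and at 1 month after palsy onset". The F-wave section gives the same window. The abstract agrees for both: "They will also undergo facial nerve electromyography and F-wave detection within 1 week after onset of" Bell's palsy.
- **Entry (Inclusion criteria):** onset no more than 2 days earlier.
- **Treatment (Acute stage):** for A and B, "The acupuncture therapy will be performed once every 2 days"; group C is not needled in this stage.
- **Later treatment:** A, B and C share electroacupuncture from day 8 (Stable and recovery stages). D receives none at any time (Western medicine treatment).
- **Order of evaluation and treatment (Table 1):** the non-acupuncture control is evaluated in the first week, before its acupuncture starts. The medicine control is evaluated in the first week after randomization. Nothing comparable is stated for A or B.

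**The concern.** A before-after comparison needs a first value that treatment has not yet touched. Here the window for that value is counted from onset and runs to the end of day 7. That is the whole acute stage, and the acute stage is the only period in which A, B and C are treated differently. In C and D the first value is free of acupuncture by design. In A and B it need not be.

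The Background section leaves open whether early electroacupuncture might worsen nerve edema and conduction. If it did so for a short time, a late first examination in group A would record the worsening as the starting point, and recovery by 1 month would look like extra improvement. If early treatment instead had a lasting benefit, part of it would already be in the starting value and the change would understate it. Separately, the two MRI limits cannot both be the rule.

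**Working it through.** The plan gives no figure to reproduce on this point, so the check is a count of sessions followed by simple algebra.

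**Inputs.** The session interval is 2 days (Acute stage). The first-examination limit L is day 7 (Methods) or day 3 (abstract, MRI only). The day of the first session, s, is not stated. Entry within 2 days of onset suggests 0 to 3, and that range is my assumption.

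**Count.** Sessions fall on days s, s+2, s+4 and so on. The number strictly before day L is (L − s)/2, rounded up.

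| First session on day | Before a day-7 examination | Before a day-3 examination |
|---|---|---|
| 0 | days 0, 2, 4, 6: 4 | days 0, 2: 2 |
| 1 | days 1, 3, 5: 3 | day 1: 1 |
| 2 | days 2, 4, 6: 3 | day 2: 1 |
| 3 | days 3, 5: 2 | 0 |

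In groups C and D the count is 0 in every row, because C starts on day 8 and D never starts. The 3-day limit reduces the exposure of the first MRI but does not remove it, and it does not apply to EMG or F-wave. If the first examination had to precede the first session, the count would be 0 in all four groups.

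**Effect on the estimate.** Let E0 be the between-arm effect already present at the first examination and E1 the effect at 1 month.

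- 1-month values alone estimate E1, so there is no bias.
- Before-after change estimates E1 − E0, so the bias is −E0.
- 1-month values adjusted for the first value with slope b estimate E1 − b·E0, so the bias is −b·E0.

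If a fraction f of a lasting effect is present at the first examination (E0 = f·E1), the change shows (1 − f)·E1. If the early effect is temporary and gone by 1 month (E1 = 0), the change shows −E0, which has the opposite sign. The documents give no value for E0 or f, so the size and direction of the bias are unknown.

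**Value of a true pre-treatment measurement.** If r is the correlation between the first and the 1-month value, adjustment changes the variance, relative to 1-month values alone, by the factor 1 − r². The documents do not give r. Over an assumed range:

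- r = 0.3: 1 − 0.09 = 0.91
- r = 0.5: 1 − 0.25 = 0.75
- r = 0.7: 1 − 0.49 = 0.51

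**The case against.** Several points on the other side stand.

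- **An upper limit is not a schedule.** An examination on day 2 before the first session complies with every passage. The flowchart (Fig. 1) is not available here and may fix the order. A reader might infer that the change is contaminated; the text supports only that it can be.
- **The named analyses may escape.** Statistical analysis says that a chi-square "test will be used to compare the edema onset frequency of the facial nerve on the affected side", and names one-way ANOVA for EMG and F-wave. No change score is named, and 1-month values compared between randomised arms are unaffected. That limits the harm to the before-after aim and to any change or baseline-adjusted analysis. It does not remove it, because that aim is the declared purpose of the repeated examinations. The choice of model may be left to an analysis plan not shown, so the absence of covariate adjustment is not itself an error.
- **A late first examination has a use.** Compared between arms, a measurement at the end of the acute stage could show whether early electroacupuncture worsens edema or conduction. It is then an outcome and not a starting value.
- **Drug treatment is common.** All four groups receive the same oral medication, so any effect of it on the first value does not differ by design between arms.

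A further inference is tempting. The Elimination criteria remove patients with brain lesions "diagnosed on the basis of skull computed tomography or MRI", so a late study MRI might seem to remove patients after randomisation. The documents do not show this. CT is allowed as well, the envelope is opened only once eligibility is verified and consent signed, and nothing says that the outcome MRI is the eliminating scan.

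**Conclusion.** The point holds as a timing defect in the secondary outcomes. As written, about 2 to 4 assigned sessions can precede the first EMG, F-wave or MRI in groups A and B (0 to 2 for MRI under the abstract's limit), against none in C and D. This assumes a first session between day 0 and day 3 and an examination at the end of its window, so it describes what the plan permits and is not an expected average. The resulting bias in before-after change is of unknown size and direction.

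For A or B against C, all of the treatment difference can fall before the first examination. Against D it is only a part, since A and B continue treatment that D never receives. The HB and Sunnybrook primary outcomes are not touched. The 3-day and 7-day MRI limits contradict each other whatever view is taken of the rest.

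**What to change.** 1. Reconcile the MRI window in the abstract with that in the Methods, so that one limit applies.
2. Schedule the first MRI, EMG and F-wave after consent and before the first assigned session in all four arms (in D, at the equivalent point), and record the dates of each examination and session.
3. Treat any first examination done after a session as an early post-treatment outcome, compared between arms. Do not use it as a baseline or as a covariate.
4. Compare 1-month values between arms with the true pre-treatment value as covariate.

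The examinations are the same ones already planned, so the cost is scheduling and a few lines of analysis text. The downside is tighter booking of the scanner and the electrophysiology laboratory. The Background stresses early initiation and the Discussion stresses avoiding delay, so treatment should not be held back for an examination; item 3 covers patients for whom the order cannot be met. For a trial already recruiting, items 3 and 4 can still be applied from the recorded dates.

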#### Facial nerve electromyography

The surface recording electrodes will be placed on the orbicularis oculi muscle and the orbicularis oris. The reference electrode will be placed on the nasal bone. The ground electrode will be placed on one arm. Super strong stimulations will be applied to the stylomastoid foramen, and the latency and amplitude of the motor evoked potentials (M wave) at the initial location will be observed, first on the unaffected side and then at the same location on the affected side. The results of the two sides will be compared. Meanwhile, the R1/M-wave ratio in latency will be measured. The measurements will be performed within 7 days and at 1 month after palsy onset.

#### F-wave detection of facial nerve

The participants will be in supine position in a silent room with constant temperature, and the examination (normally right side first) will be performed after 5 minutes of relaxation. An electromyogram evoked potential test (Dantec Keypoint; Alpine Biomed, Skovlunde, Denmark) will be performed. The surface electrodes will be placed on the orbicularis oculi muscle and the depressor anguli oris muscle, and the stimulus (20 times of square wave with a time history of 0.3 ms, firing frequency of 1 Hz) will be applied on nervi auriculares anteriores. After the stimulating current strength is gradually increased to approximately 120–130 %, with a filtering range of approximately 100–5000 Hz and analysis duration of 50 ms, the presence of F waves in the affected and unaffected sides and the relevant data will be recorded. The measurements will be performed within 7 days and at 1 month after palsy onset.

### Statistical analysis

In this study, statistical analyses of data will be performed by professionals rather than investigators using intention-to-treat and per-protocol approaches. All demographic and clinical characteristics of the subjects (such as sex, age) will be processed based on descriptive analyses. Quantitative data will be presented as average, standard deviation, median value, and range. Qualitative data will be presented as the frequency and percentage.

For the primary outcome measurements, a repeated-measures multifactorial analysis will be performed to identify differences between groups (differences within each group based on time, and the effects of the interaction of the variables based on group) to compare the differences in HB and Sunnybrook score changes between the interventional and control groups based on time (baseline, every treatment time and 1 month after palsy onset). The period from the onset to the first change in facial paralysis evaluation scale score in and the patients’ overall recovery period will be compared using one-way analysis of variance (ANOVA) between all groups. For the secondary outcome measurements, a χ^2^ test will be used to compare the edema onset frequency of the facial nerve on the affected side. One-way ANOVA will be applied to identify differences in results of facial nerve electromyography and F-wave detection between groups. In cases of non-normally distributed data, the Kruskal-Wallis H test will be performed.

All adverse events reported during the study will be included in the clinical report, and the prevalence of adverse events will then be calculated. The percentage of participants with adverse events in each group will be calculated and compared using the χ^2^ test or Fisher’s exact test. Statistical analyses will be performed using IBM SPSS for Windows version 19.0 statistical software (IBM, Armonk, NY, USA). All the tests will be two-sided, and a *P* value <0.05 will be considered statistically significant.

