### Sample size calculation

Count data of the parallel controlled trial (1:1) will be analyzed statistically using a two-sided superiority test where α = 0.05, power = 90 %. The formula used for calculation is as follows:$$ n=\frac{{\left({Z}_{1-a}+{Z}_{1-\upbeta}\right)}^2\times \left({\sigma}_1^2+{\sigma}_2^2\right)}{\delta^2} $$

It is assumed that the change in the standard deviation of the Sunnybrook facial grading system score before and after the treatment in the control group is 10 points and that that in the treatment group is 18 points. A change will be considered clinically significant if the change of Sunnybrook scale score before and after the treatment in the treatment group is 13 points higher than that in the control group. The estimated sample size is arrived at as follows:$$ n=\frac{{\left({Z}_{1-a}+{Z}_{1-\upbeta}\right)}^2\times \left({\sigma}_1^2+{\sigma}_2^2\right)}{\delta^2}=\frac{{\left(1.96+1.28\right)}^2\times \left({10}^2+{18}^2\right)}{13^2}\approx 26.33 $$

It is assumed that the change in the standard deviation of HB scale score before and after the treatment in the control group is 1 point and that that in the treatment group is 3 points. A change will be considered clinically significant if the change of HB scale score before and after the treatment in the treatment group is 2 points higher than that in the control group. The estimated sample size is arrived at as follows:$$ n=\frac{{\left({Z}_{1-a}+{Z}_{1-\upbeta}\right)}^2\times \left({\sigma}_1^2+{\sigma}_2^2\right)}{\delta^2}=\frac{{\left(1.96+1.28\right)}^2\times \left({1}^2+{3}^2\right)}{2^2}=26 $$

It is determined that there should be at least 27 patients in each group. The dropout rate is considered to be 20 %, and thus at least 33 patients should be enrolled in each group. Hence, a total of 132 patients are required to conduct this study.

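### The primary repeated-measures analysis uses treatment sessions as its time factor, so its time points differ between arms and can go missing because a patient has recovered

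*Protocol article*

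**What the plan says.** The Statistical analysis section plans that "a repeated-measures multifactorial analysis will be performed to identify differences between groups". Its purpose is to "compare the differences in HB and Sunnybrook score changes between the interventional and control groups based on time", with baseline, each treatment session and 1 month after palsy onset as time levels. Analyses are to be both intention-to-treat and per-protocol, in SPSS 19. No procedure is named for the repeated-measures analysis and no variance assumption is given.

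Other sections determine when those scores exist:

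- **Abstract, Methods/Design:** scores are taken at each treatment visit, and acupuncture continues "until the patients recover or withdraw from the study". Stable and recovery stages repeats that stopping rule.
- **Acute stage; Stable and recovery stages:** groups A and B are treated in the acute stage. Group C starts acupuncture on day 8 after onset.
- **Western medicine treatment:** group D receives no acupuncture at any time.
- **Table 1:** 12 sessions, three a week for four weeks. The two control arms complete evaluations in the first week, with no days given.
- **Primary outcome:** the late score falls in the first month after therapy, whereas Statistical analysis dates it from onset.

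Sample size calculation assumes unequal SDs of change. For Sunnybrook the SD "in the control group is 10 points and that that in the treatment group is 18 points"; for House-Brackmann it is 1 and 3.

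**The concern.** A repeated-measures analysis needs time points that mean the same thing in every arm. Here the n-th session falls on a different day after onset in group C than in groups A and B, and it has no stated meaning in group D. The group-by-time term would then mix treatment effect with time since onset, in a condition that improves over time.

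The number of scores per patient also depends on the outcome. A patient who recovers early stops attending for treatment, so the later sessions are empty for that patient. If treatment speeds recovery, these gaps are most frequent in the best arm. An analysis restricted to complete series would remove the best results, mostly from that arm, and pull the difference towards zero.

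Two smaller matters concern precision and standard errors. Baseline enters as a time level and through change scores, not as a covariate. The analysis text also makes no allowance for the unequal SDs used in planning.

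**Working it through.** **1. The plan's own figure.** The inputs are a "two-sided superiority test where α = 0.05, power = 90"%, with a Sunnybrook difference of 13 and a House-Brackmann difference of 2.

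- Sunnybrook: (1.96 + 1.28)² × (10² + 18²) / 13² = 10.4976 × 424 / 169 = 26.34
- House-Brackmann: 10.4976 × (1² + 3²) / 2² = 26.24

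Both round up to the stated 27 per group. Then 27 × 1.2 = 32.4, giving 33 per group and 132 in total, as stated.

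**2. Which scores exist, by arm.**

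| Arm | Acupuncture begins | Acupuncture ends |
|---|---|---|
| A, B | acute stage | recovery or withdrawal (text); 12 sessions (Table 1) |
| C | day 8 | same conflict |
| D | never | not applicable |

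The 1-month score is the only late time point that does not depend on sessions, and its date differs between Primary outcome and Statistical analysis. For a patient who stops at recovery, 1 month after therapy and 1 month after onset are different days.

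**3. Attenuation if incomplete series are dropped.** The documents give no baseline distribution, mean gain or recovery rate, so all of these are assumed.

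*Illustration 1.* Baseline 45 (SD 10); mean gain 45 (SD 18) on treatment and 32 on control; scores capped at 100; everyone who reaches 100 is removed.

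- Control SD 10: 31% and 5% recover. The difference falls from 9.16 to 5.68, a loss of 38%.
- Control SD 18: the difference falls from 10.21 to 8.75, a loss of 14%.

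*Illustration 2.* Baseline 50 (SD 12); linear change over 12 visits; SDs of change 18 and 10; treatment gain 13 above control; recovery at 95 or more; only those recovered before the last visit are removed.

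| Control mean gain | Recovered early, treatment / control | Full difference | After removal | Loss |
|---|---|---|---|---|
| 15 | 18.1% / 2.3% | 11.29 | 8.72 | 23% |
| 25 | 31.9% / 8.2% | 9.40 | 6.39 | 32% |
| 32 | 43.6% / 16.4% | 7.55 | 4.65 | 38% |

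The full differences are below 13 because of the scale ceiling.

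**4. Baseline as covariate.** With equal variances at baseline and follow-up and correlation ρ, the variance ratio of change score to ANCOVA is 2(1 − ρ)/(1 − ρ²) = 2/(1 + ρ). This is 1.67, 1.33 and 1.11 at ρ = 0.2, 0.5 and 0.8. The documents do not give ρ. Under randomisation both estimators are unbiased.

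**5. A common residual variance.** The documents do not map the planning SDs to four arms. Assume A–C have the larger SD, D the smaller, and n is equal.

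- Sunnybrook pooled variance: (3 × 324 + 100)/4 = 268
- A vs B: SE ratio √(268/324) = 0.909; error 2[1 − Φ(1.96 × 0.909)] = 0.075
- A vs D: SE ratio √(2 × 268/424) = 1.124; error 0.028; power at 27 per group 0.859 instead of 0.907
- House-Brackmann, pooled variance (3 × 9 + 1)/4 = 7: A vs B 0.084, A vs D 0.020

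If C and D both have the smaller Sunnybrook SD, the pooled variance is (2 × 324 + 2 × 100)/4 = 212. A vs B is then 0.113 and A vs D 0.050. With only D smaller, the simulated four-arm omnibus test is 0.055 (Sunnybrook) and 0.059 (House-Brackmann). Point estimates do not change.

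**The case against.** A reader might infer that the plan loses its recovered patients, ignores baseline and pools variances, so that its effects and error bars are wrong. The document does not support that reading.

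- **Deletion.** Listwise deletion follows only from a complete-case procedure, and none is named. The section uses the term ANOVA for other outcomes, promises intention-to-treat, and SPSS 19 does not settle the choice. An article may leave missing-data handling to a fuller plan. A 1-month score is planned with no exception for recovered patients, so it is mainly their intermediate scores that are at risk. Table 1's 12 sessions, if they governed, would give the acupuncture arms a fixed number of sessions.
- **Baseline.** It is used, as a time level and in the changes. Leaving it out as a covariate costs precision and causes no bias.
- **Variances.** No pooling is stated and the mapping of SDs to arms is an assumption. Even if pooling occurred, it would be conservative for A vs D in the pattern above and would hardly move the omnibus test.

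All of this stands. It does not remove the defect in the time factor, which the article itself fixes. Group D still has no acupuncture sessions, group C still starts later, and the sections still disagree on how long sessions continue and when the late score is taken. A mixed model would keep recovered patients, but session number would still not be a common clock, and the model would have to extrapolate beyond recovery. Fig. 1 was not available for this check; if it lists assessment days, the text should state them.

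**Conclusion.** The point holds in limited form. The time factor of the primary analysis is not common to the four arms, and the availability of scores depends on the outcome. This follows from the article's own text and needs no assumption.

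The consequence is conditional. If incomplete series are dropped, the Sunnybrook difference is attenuated by about 14–38% in the scenarios tried, and the analysis is not intention-to-treat. That range rests on assumed baselines, gains, SD patterns and recovery thresholds; it illustrates the risk and does not estimate a bias in this trial.

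The baseline covariate is a precision gain only: change-score variance is 1.1–1.7 times the ANCOVA variance for correlations from 0.8 down to 0.2. A common variance would distort pairwise error rates, for example about 0.075 for A vs B and 0.028 for A vs D if only group D has the smaller SD. It would not distort the estimates.

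**What to change.** 1. **Reconcile the schedule.** Abstract, Table 1, Stable and recovery stages, Primary outcome and Statistical analysis must agree on when sessions end and when the late score is taken. How long treatment should last is not a matter for this review.
2. **Replace session number by common days from onset** for all four arms, including group D.
3. **Name the model.** Use a linear mixed model (available as SPSS MIXED) on post-baseline scores in all randomised patients, with group, day, group-by-day and baseline score as covariate. Allow arm-specific residual variances for the pairwise contrasts.
4. **State what happens after recovery.** Carry the recovered score forward to 1 month after onset, or use the planned 1-month score. Report the adjusted 1-month difference.

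**Cost.** Items 3 and 4 are mostly wording and use data already planned. Carrying forward assumes no relapse before 1 month; using the planned 1-month score avoids that assumption but requires recovered patients to attend. Item 2 may add scoring visits, chiefly in group D, and so goes beyond analysis wording. Making the 1-month difference the main contrast also narrows the primary question and should be declared as such.
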